##### Procedure for unblinding if needed {17b}

There are no circumstances where emergency unblinding would be absolutely essential for further management of the patient. Any clinical deterioration or need for repeat surgery would terminate the patient’s participation in the study.

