### Data collection and management

#### Plans for assessment and collection of outcomes {18a}

##### Primary outcome

The overall primary clinical outcome is the recurrence of CSDH within 90 days after the initial surgery and drainage. Recurrence is defined as neurological deterioration leading to hospitalization, confirmed recurrent CSDH on cranial imaging (e.g., CT/MRI), and a need for repeat surgery. A retrospective review of the electronic medical record will be used to clarify whether the patient has experienced a recurrence.

Recurrence or no recurrence will be registered in REDCap by a member of the research team after 90 days.

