##### Secondary outcomes

A retrospective review of the electronic medical record will be used to clarify whether the patient has died during the observation period, and if so, for what reason.

The Modified Rankin Scale (mRS) is a clinician-reported measure of the patient’s degree of disability. It is widely applied for evaluating the outcome for stroke patients and as an endpoint in most randomized clinical trials [15]. It is a 7-level scale covering the entire range of functional outcomes from no symptoms to death. There is extensive evidence for the validity of the mRS, and the mRS categories correlate with the functional outcomes within the spectrum of stroke pathologies [16]. The limitations of the mRS are the subjective assignment of categories and the reproducibility of the score by examiners and patients [17]. A systematic review and meta-analysis of studies describing interobserver variability of the mRS reported pooled reliability (across 10 studies, *n* = 587 patients) of *κ* = 0.46 and a weighted *κ* of 0.90 [18]. To reduce interobserver variability, all members of the research group will be certified in the use of the mRS (http://rankinscale.org/).

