#### Plans to promote participant retention and complete follow-up {18b}

The time to follow-up is 90 days, which we believe is a sufficiently short follow-up period to minimize patient attrition and maximize the completeness of data collection. Most symptomatic recurrent CSDH cases related to the primary operation are expected to occur within this time frame [22]. The primary outcome data (CSDH recurrence at 90 days) will be obtained through the electronic medical record. To limit participant burden related to follow-up visits, we will contact each participant by phone after 90 days. Here, we will assist the patient in completing the SF-36 questionnaire (which they will have received via e-mail/E-boks) and determine the mRS category. If a member of the research team assesses that it is not possible to obtain a valid assessment over the telephone, the patient and their relatives are offered attendance at the outpatient clinic.

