#### Overall objectives and background

Regardless of the choice of surgical procedure, there is a risk of spontaneous recovery/recurrence of the hematoma. Patients who develop recurrence experience significantly greater morbidity and mortality than patients who are cured after the first operation. In recent years, there has been an increasing interest in the composition of the hematoma fluid and in the systemic response as it is likely that the causes of hematoma expansion and recurrence will be found here. Therefore, we will collect hematoma fluid and hematoma membrane during the operation and will collect fluid from the drainage bag when the drain is removed after 6, 12, or 24 h. Furthermore, a blood sample before and after the operation will be obtained for the investigation of systemic changes. The biological material will be used for the analysis of pro- and anti-inflammatory as well as vascular (blood vessel-associated) proteins and peptides. A study of specific neurons and glia (markers of brain impact) will also be performed.

We hope that the study results will shed light on some of the crucial cerebral and systemic processes behind hematoma expansion and whether elimination (leaching) of particular proteins and peptides during surgery influences recurrence risk and postoperative neurological status. Finally, we hope to identify markers that can predict the risk of recurrence.

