### Methods in analysis to handle protocol non-adherence and any statistical methods to handle missing data {20c}

Loss to follow-up is expected to be rare, and analyses will be done as complete case analyses. All outcomes will be analyzed using intention-to-treat analyses. For the primary outcome, this will be supplemented by an as-treated sensitivity analysis in which the observed drainage times will be used as a continuous covariate instead of the randomly assigned drainage times.

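### The protocol ends study participation at deterioration or repeat surgery, the events that define recurrence; this contradicts its planned day-90 follow-up and puts mRS and SF-36 at risk for patients who recur

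*Protocol article*

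**What the plan says.** All references are to the protocol article.

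- **Procedure for unblinding {17b}:** "Any clinical deterioration or need for repeat surgery would terminate" the patient's participation.
- **Criteria for discontinuing or modifying allocated interventions {11b}:** gives situations in which discontinuation may happen. Deterioration counts only where it leads to repeat surgery or craniotomy within the primary admission. The section title refers to the intervention, but its text speaks of leaving the study.
- **Primary outcome {18a}:** "Recurrence is defined as neurological deterioration leading to hospitalization, confirmed recurrent CSDH on cranial imaging (e.g., CT/MRI), and a need for repeat surgery". Also: "Recurrence or no recurrence will be registered in REDCap by a member of the research team after 90 days".
- **Secondary outcomes {18a}:** "A retrospective review of the electronic medical record will be used to clarify whether the patient has died during the observation period". The list in Outcomes {12} gives recurrence as one possible cause of death.
- **Retention and follow-up {18b}:** "we will contact each participant by phone after 90 days". This call yields the mRS category and the assisted SF-36.
- **Non-adherence and missing data {20c}:** every outcome is analysed by intention to treat, loss to follow-up is expected to be rare, and "analyses will be done as complete case analyses".

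No section says whether outcome collection continues after participation ends under {17b}.

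**The concern.** The trigger in {17b} is almost the same as the primary event. A patient cannot meet the recurrence definition without deteriorating and needing repeat surgery, so each recurrence also meets the rule that ends participation. A site that takes this at face value would not make the 90-day call to a patient who has recurred.

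The patients lost would not be a random subset. The protocol's biobank section says: "Patients who develop recurrence experience significantly greater morbidity and mortality than patients who are cured after the first operation". Leaving them out of mRS and SF-36 conditions those comparisons on something that happens after randomisation and that drainage time may affect. The Discussion gives mRS and SF-36 the task of showing the wider effect of shorter drainage on function and quality of life, and {20a} tests each short arm against 24 h on them. If a short arm recurs more often, the harm done by those extra recurrences would be missing from both.

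**Working it through.** **1. The passages side by side**

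| Question | {17b} | {11b} | {18a}, {18b}, {20c} |
|---|---|---|---|
| Does recurrence after discharge end participation? | Yes, read literally | Not listed | No: recurrence is registered after 90 days and everyone is phoned |
| Does repeat surgery in the primary admission end it? | Yes | It may | No: same follow-up, analysed as randomised |
| Is loss to follow-up rare? | Not if every recurrence leaves | Depends on the number of in-hospital reoperations (not given) | Yes, expected |

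The three columns cannot all be applied to the same patient.

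**2. Inputs, all from Sample size {14}**

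Recurrence p = 0.163 in all arms, margin m = 0.07, final-stage one-sided alpha 0.025, final-stage power 0.95, maximum 724 per arm and 2172 in total.

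**3. Reproducing the plan's final-stage size**

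n = (z₀.₉₇₅ + z₀.₉₅)² × 2p(1 − p) / m²
= (1.960 + 1.645)² × 2 × 0.163 × 0.837 / 0.07²
≈ 12.99 × 55.69 ≈ 723.6, so 724 per arm. This matches the plan.

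**4. Patients removed by {17b}, read literally, through recurrence alone**

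- Per arm at the planned rate: 724 × 0.163 = 118.
- All three arms: 2172 × 0.163 = 354.
- At the plan's expected total of 1928 when all arms have the planned rate: 1928 × 0.163 = 314.
- An arm at the margin: 0.163 + 0.07 = 0.233, and 724 × 0.233 = 169.

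As shares, 16.3% of an arm would lack the day-90 call, or 23.3% of an arm at the margin. Neither fits an expectation that loss is rare. These are upper figures for loss through recurrence. If {11b} governs, only reoperations in the primary admission count, and the documents give no rate for those.

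**5. What a complete-case comparison would miss (illustration)**

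Assumptions not in the documents: recurrence worsens mRS by d points on average, with d between 0.5 and 2, and patients without recurrence have the same mean mRS, a, in both arms.

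- Everyone included: arm mean = a + r × d, where r is the recurrence rate. Difference between arms = (0.233 − 0.163) × d = 0.07d, which is 0.035 at d = 0.5 and 0.14 at d = 2.
- Patients without recurrence only: a − a = 0.

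Under these assumptions the whole difference that acts through recurrence disappears.

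**The case against.** The strongest reply is that {17b} is one sentence in the unblinding section, there to explain why emergency unblinding is unnecessary. The section written for discontinuation is {11b}, which is permissive and limited to the primary admission. Most of the protocol assumes that patients who recur stay under observation: recurrence is registered after 90 days, patients with recurrence are described separately {20b}, everyone is phoned, and analysis is by intention to treat. This stands as far as it goes. The cut-off of mRS and SF-36 is a consequence of following {17b}, not something the protocol announces. It does not remove the contradiction, because {11b} does not say that it overrides {17b}, and it too describes leaving the study.

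A reader might infer that 90-day mortality is also cut off. The documents do not support this. Death and its cause are taken from the medical record without patient contact, and deaths related to recurrence are explicitly to be counted. The primary outcome is likewise read from the record. Deaths found there could also be scored as mRS 6, which would narrow the mRS gap to survivors of recurrence.

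A reader might also infer that the bias always favours the short arms. It does so only if short drainage raises recurrence, which is what the trial is testing. Under the assumptions above it hides harm; it does not by itself create an apparent benefit.

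The figure of 169 needs an arm exactly at the margin to reach the last stage. With the non-binding stopping guidelines followed, such an arm passes stage 4 with probability of at most about 0.1. Part of any SF-36 loss has a separate, stated cause: {26a} treats patients who are incapacitated at 90 days as lost for SF-36, and correcting {17b} would not recover them.

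Leaving the matter to an analysis plan would not be enough, because no analysis recovers a call that was never made.

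**Conclusion.** The point holds as an internal contradiction with a real consequence for two secondary outcomes. Read literally, {17b} removes every patient with the primary event from the day-90 contact, against {18a}, {18b} and {20c}, and it also disagrees with {11b}. If sites follow it, mRS and SF-36 are compared mainly among patients without recurrence. The loss is up to about 118 of 724 per arm at the planned 16.3%, and up to 169 of 724 in an arm at the 7-point margin. Both counts assume the literal reading and the maximum sample size; they are lower if {11b} governs or if sites phone everyone regardless. The mRS shift of 0.035 to 0.14 rests wholly on the assumed effect of recurrence.

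The primary outcome and mortality are not affected as planned. Correction matters now because Trial status reports that recruitment is under way, and day-90 mRS and SF-36 not collected on time may be lost for good.

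**What to change.** Reconcile {11b} and {17b} with each other and with {18a}, {18b} and {20c}. State once, and refer to it in each section, that:

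- clinical deterioration, repeat surgery or stopping the allocated drainage does not end outcome follow-up;
- recurrence, mRS, SF-36, mortality and complications are collected as scheduled up to day 90 and analysed in the randomised arm;
- only withdrawal of consent to data collection ends follow-up.

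In {11b}, separate stopping the allocated drainage from leaving the study. Clinical management, including the handling of the drain, is unchanged.

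The cost is a few sentences and a reminder to the four departments, since the 90-day call and the record review are already planned for every participant. Section {25} says that no protocol changes will be made, so this would have to be issued as a clarification or an exception to that statement. For patients already recruited, the sites should check whether anyone who recurred was left out of the 90-day contact, and report the number by arm.

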### Data collection and management

#### Plans for assessment and collection of outcomes {18a}

##### Primary outcome

The overall primary clinical outcome is the recurrence of CSDH within 90 days after the initial surgery and drainage. Recurrence is defined as neurological deterioration leading to hospitalization, confirmed recurrent CSDH on cranial imaging (e.g., CT/MRI), and a need for repeat surgery. A retrospective review of the electronic medical record will be used to clarify whether the patient has experienced a recurrence.

Recurrence or no recurrence will be registered in REDCap by a member of the research team after 90 days.

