##### Sample size calculations

The MAMS design required the choice of a number of stages together with the choice of stage-specific decreasing significance levels together with stage-specific power levels, which result in an overall power and a familywise error rate. To inform this decision, we calculated several different designs considering two up to five stages. Stage-specific design parameters were in a try-out manner picked such that the overall power and FWER were approximately equal to 0.8 and 0.028, respectively. Especially, stage-specific significance levels for the initial stage of 0.5, 0.3, and 0.2 were considered. The final design choice was obtained from balancing the resulting expected sample sizes (for different numbers of non-inferior treatment arms) with a greater weight on the sample size in absence of non-inferior treatment arms. This resulted in a final design with five stages and decreasing stage-specific significance levels of alpha = 0.5, 0.3, 0.2, 0.1, and 0.025 together with stage-specific power levels of 0.9 for the first three stages and 0.95 for the last two stages. Stage parameters were chosen such that the overall power for the final comparison of each experimental arm (6 h or 12 h drainage) to control (24 h drainage) is approximately equal to 0.8. The familywise error rate corresponding to the design is approximately 0.028.

Assuming a recurrence rate of 16.3% on the basis of previous DACSUHS studies in all treatment arms (both experimental and control), equal allocation to all treatment arms, and a non-inferiority margin of 7%, we obtained the following cumulative sample sizes.

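### The recurrence definition and the rules ending participation leave it open whether a reoperation during the primary hospital stay counts as a primary event

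*Protocol article*

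**What the plan says.** All references are to the protocol article.

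- **Window (Primary outcome, {18a}):** "The overall primary clinical outcome is the recurrence of CSDH within 90 days after the initial surgery and drainage". The clock starts at the operation, not at discharge.
- **Definition (same section):** "Recurrence is defined as neurological deterioration leading to hospitalization, confirmed recurrent CSDH on cranial imaging (e.g., CT/MRI), and a need for repeat surgery".
- **Source (same section):** "A retrospective review of the electronic medical record will be used to clarify whether the patient has experienced a recurrence".
- **Discontinuation (section {11b}):** the list of reasons for discontinuing the study after randomization includes deterioration that needs repeat surgery or craniotomy in the primary stay. It also includes signs of infection at the drain, pronounced leakage, and withdrawal at the request of the patient or a relative.
- **Termination (Procedure for unblinding, {17b}):** "Any clinical deterioration or need for repeat surgery would terminate the patient’s participation in the study". This is not limited to the primary stay.
- **Analysis (section {20c}):** "All outcomes will be analyzed using intention-to-treat analyses", but also "Loss to follow-up is expected to be rare, and analyses will be done as complete case analyses". The secondary-outcomes text in {20a} repeats intention-to-treat.

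**The concern.** The trial varies only the drainage time. A hematoma that re-accumulates soon after drain removal and needs a second operation before discharge is the event most directly tied to draining for too short a time. The definition asks for a deterioration that caused an admission, and this patient was already admitted. Two other sections then end the patient's participation because of the same reoperation. Read literally, {17b} ends participation for every patient who reaches the primary endpoint.

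If such patients are scored as free of recurrence, or dropped as incomplete cases, events disappear from a non-inferiority comparison judged against a fixed absolute margin. Losing events usually shrinks the observed difference and so raises the chance of a false non-inferiority claim. The same outcome also drives every interim decision to drop an arm. Ward staff know the arm from 6 h onwards, and a research team member registers recurrence. An ambiguous definition would therefore be applied by people who may know the allocation.

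**Working it through.** **1. One patient against each rule.** Take a patient who deteriorates during the primary stay, has a recurrent hematoma confirmed on imaging, and is reoperated before discharge.

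| Rule | Result |
|---|---|
| 90 days from initial surgery ({18a}) | inside the window |
| Imaging confirmation and repeat surgery ({18a}) | met |
| Deterioration that caused an admission ({18a}) | not literally met |
| Discontinuation list ({11b}) | study discontinued |
| Termination rule ({17b}) | participation ended |
| Intention-to-treat ({20a}, {20c}) | stays in the analysis |
| Complete-case ({20c}) | dropped if the outcome is treated as missing |

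Three codings are possible: event, non-event and missing. The article does not choose among them.

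**2. The plan's own sample size.** Inputs from Sample size {14}: recurrence 16.3% in all arms, margin 7 points, final one-sided alpha 0.025, final-stage power 0.95.

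n = 2 × 0.163 × 0.837 × (1.960 + 1.645)² / 0.07² = 723.6, which gives 724 per arm as stated.

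Passing all five stages (correlation between stages √(n_i/n_j), cumulative sizes 91, 182, 344, 477, 724) gives overall power 0.802, against about 0.8 stated.

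**3. Error at the margin when all events count.** True rates are 16.3% (24 h) and 23.3% (short arm). With d the observed difference,

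P(declare non-inferiority) = Φ((0.07 − d)/SE − 1.960), SE = √{[p_c(1 − p_c) + p_t(1 − p_t)]/724}.

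With d = 0.07 this is Φ(−1.960) = 0.025. With stages followed it is 0.015. Both agree with the article's statement that 0.025 is an upper bound.

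**4. Same share of recurrences uncounted in every arm.** The shares are assumptions.

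| Share lost | p_c | p_t | d | SE | Final test | Stages followed |
|---|---|---|---|---|---|---|
| 10% | 0.1467 | 0.2097 | 0.063 | 0.0201 | 0.054 | 0.032 |
| 20% | 0.1304 | 0.1864 | 0.056 | 0.0191 | 0.110 | 0.068 |
| 30% | 0.1141 | 0.1631 | 0.049 | 0.0181 | 0.212 | 0.136 |

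**5. Net loss in the short arm only.** These are excess early failures, with control fixed at 16.3%. One point is 0.01 × 724 ≈ 7 patients. The last two columns are final-test error.

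| Points lost | Patients of 724 | Scored as no recurrence | Dropped from the analysis |
|---|---|---|---|
| 1 | about 7 | 0.070 | 0.056 |
| 2 | about 14 | 0.163 | 0.115 |
| 3 | about 22 | 0.315 | 0.212 |

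With stages followed, the scored-as-no-recurrence column becomes 0.043, 0.102 and 0.208.

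**6. A larger share lost in control.** The Trial rationale expects shorter stays with shorter drainage. A failure at a given hour may then fall after discharge in a short arm, where it counts, but within the stay in the 24 h arm.

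- 10% lost in the short arm and 20% in control: d = 0.2097 − 0.1304 = 0.0793, P ≈ 0.007.
- 20% and 30% lost: d = 0.1864 − 0.1141 = 0.0723, P ≈ 0.019.

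Both are below 0.025, so here the error works against non-inferiority.

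**The case against.** The strongest reply is that the article, read as a whole, counts these patients. The window opens at the operation. The outcome comes from the medical record, which needs no further participation. Intention-to-treat applies to all outcomes. Section {11b} sits under a heading about allocated interventions, and {17b} is a remark on emergency unblinding, so neither defines an analysis set. Complete-case analysis is tied to loss to follow-up, and a reoperated patient has a known outcome. Because recurrence is analyzed as a binary outcome, ending participation once it has occurred loses no primary information. Patients discontinued for infection or leakage also keep a record-based outcome.

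Much of this stands. No section calls an in-stay reoperation a non-event or removes discontinued patients, and the article gives no in-stay share. The arm-dependent stay in step 6 can reverse the direction. The figures in step 4 also need the fixed 7-point absolute margin. The planned effect measure is the relative risk, and equal proportional loss leaves that at 0.233/0.163 = 1.43.

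The reply does not remove the conflict. The definition still requires a deterioration that caused an admission, and both {11b} and {17b} speak of leaving the study, not only the allocated drainage. This is not a detail left to an analysis plan: the article states the endpoint and the discontinuation rules itself, and they disagree.

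**Conclusion.** The point holds as a conflict in the endpoint and follow-up rules that permits early drainage failures to go uncounted. A reader might infer that in-stay reoperations are excluded and that the trial is therefore biased towards non-inferiority. The documents do not support that: the exclusion is nowhere stated, and the 90-day window, record review and intention-to-treat analysis allow a reading with no bias at all.

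If the events are lost, the effect is material. Against the fixed 7-point margin, an assumed equal loss of 10–30% in all arms raises the final-test error from 0.025 to about 0.05–0.21, or from 0.015 to about 0.03–0.14 with stages followed. Uncounted excess early failures in a short arm act in the same direction. Arm-dependent length of stay could act either way. All shares are assumptions, so the article does not allow the true size, or a certain net direction, to be stated.

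**What to change.** - **Endpoint ({18a}):** define the primary event as imaging-confirmed recurrent CSDH with repeat surgery at any time from the index operation to day 90, whether in the primary stay or after readmission.
- **Follow-up and analysis ({20c}):** state that patients discontinued under {11b} or {17b} remain in the intention-to-treat set, with the 90-day outcome taken from the record review unless consent is withdrawn, and that a reoperated patient is an event, not a missing value.
- **Consistency:** reconcile {11b} and {17b} with {18a} and {20c}, including their different scope. This concerns outcome counting and follow-up only; no clinical stopping rule needs to change.

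The cost is wording in the protocol, the analysis plan and the case report form, plus re-checking the records of patients already discontinued. The 90-day record review is already planned. The article says that the protocol will not be changed, so the clarification needs a documented amendment.

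### The recurrence definition cannot literally be met before first discharge, and the exit rules end participation at repeat surgery, so recurrences reoperated during the primary stay may not be counted in the non-inferiority test

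*Protocol article*

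**What the plan says.** All references are to the protocol article.

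- **Window** (Primary outcome, under {18a}): "The overall primary clinical outcome is the recurrence of CSDH within 90 days after the initial surgery and drainage". The primary stay is not carved out.
- **Event** (same paragraph): "Recurrence is defined as neurological deterioration leading to hospitalization, confirmed recurrent CSDH on cranial imaging (e.g., CT/MRI), and a need for repeat surgery". All three conditions must hold.
- **Exit rule 1** ({11b}): among the situations in which the study can be discontinued after randomization is a deterioration during the primary admission that makes another operation necessary.
- **Exit rule 2** ({17b}): "Any clinical deterioration or need for repeat surgery would terminate the patient’s participation in the study". This one has no time limit.
- **Data source** ({18b}): "The primary outcome data (CSDH recurrence at 90 days) will be obtained through the electronic medical record".
- **Analysis** ({20c}): "Loss to follow-up is expected to be rare, and analyses will be done as complete case analyses". The same section adds: "All outcomes will be analyzed using intention-to-treat analyses".

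No section says whether a reoperation for recurrent hematoma before first discharge is a primary event, or whether patients who meet an exit rule are still followed to day 90.

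**The concern.** The window includes the primary stay, but the hospitalization condition, taken literally, shuts it out: someone who has not been discharged cannot deteriorate into a hospitalization. The exit rules point the same way, because they treat a core part of the primary event as the end of participation.

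The experimental factor is drain removal at 6 or 12 h instead of 24 h. Re-accumulation soon after removal is a plausible direct failure of a short drainage time, and some of it may appear before discharge. In a non-inferiority comparison, uncounted events shrink a real difference and so tend to make a worse arm look acceptable. The interim analyses use the same outcome and margin, so any miscounting would enter them too.

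**Working it through.** **1. Reproduce the plan's figure.** Inputs from Sample size {14}: 16.3% in all arms, margin 0.07, final one-sided alpha 0.025, final-stage power 0.95.

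n = 2 × 0.163 × 0.837 × (1.960 + 1.645)² / 0.07² = 723.6, so 724 per arm, as stated.

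**2. What can happen to a recurrence reoperated before first discharge.**

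| Handling | Support in the text |
|---|---|
| Counted | 90-day window from surgery; record review; intention-to-treat |
| Registered as no recurrence | Literal hospitalization condition |
| Treated as incomplete | Exit rules in {11b} and {17b} together with complete-case analysis |

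**3. Size of the effect if events are not counted.** The documents give no share of recurrences reoperated in the primary stay, so f below is an assumption. True rates are set at the margin: 0.163 (24 h) and 0.233 (short arm). With observed rates c and e and difference d = e − c,

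SE = √[c(1 − c)/n + e(1 − e)/n], and type I error = Φ((0.07 − d)/SE − 1.96).

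With nothing lost, d = 0.07 and the error is 0.025.

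*Share f lost in both arms, coded as non-events:* c = 0.163(1 − f), e = 0.233(1 − f), n = 724.

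| f | c | e | d | SE | Type I error |
|---|---|---|---|---|---|
| 5% | 0.1549 | 0.2214 | 0.0665 | 0.0205 | 0.037 |
| 10% | 0.1467 | 0.2097 | 0.0630 | 0.0200 | 0.054 |
| 20% | 0.1304 | 0.1864 | 0.0560 | 0.0191 | 0.110 |

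*Same share, patients dropped:* c = 0.163(1 − f)/(1 − 0.163f), e = 0.233(1 − f)/(1 − 0.233f), with n reduced accordingly.

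| f | d | Type I error |
|---|---|---|
| 5% | 0.0678 | 0.032 |
| 10% | 0.0656 | 0.041 |
| 20% | 0.0607 | 0.068 |

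*Loss in the short arm only:* 1 percentage point (0.01 × 724, about 7 patients) gives 0.070 coded as non-events, or 0.056 dropped.

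**4. When there is no bias, or it runs the other way.**
- Equal arms, equal loss: the difference stays at zero. With f = 10% both arms show 0.1467 and final-stage power moves from 0.950 to 0.964.
- Truly equal arms with more loss under 24 h, for example 2 points hidden there and 1 point in the short arm: observed 0.143 vs 0.153, SE 0.0187, power Φ((0.07 − 0.01)/0.0187 − 1.96), about 0.895 instead of 0.950.

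**The case against.** The strongest reply is that these events will be counted anyway. The window opens at surgery without exception, the outcome comes from the medical record and needs no continued participation, and intention-to-treat keeps every randomized patient in the analysis. Read literally, the {17b} sentence would end participation at every post-discharge recurrence as well and so defeat the endpoint, so it can hardly be meant as an analysis exclusion. {11b} is headed as concerning the allocated intervention.

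Much of this stands. A reader might infer that early recurrences certainly drop out and that the test is therefore biased. The documents do not support that, because the counted reading is open. The complete-case route is the weaker one: the sentence is about loss to follow-up, and a patient whose reoperation is on record has a known outcome. A reader might also extend the problem to patients transferred elsewhere. That is doubtful, since returning to a neurosurgical department for repeat surgery is naturally read as a new hospitalization. Nor is every in-stay reoperation a recurrence; the {11b} ground could cover other surgical complications.

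What does not stand is that intention-to-treat settles the matter. It fixes who is analysed and in which arm, not whether an event meets the definition. A retained patient would still be registered as having no recurrence under the literal wording. The record review finds the reoperation, but whoever enters the outcome must still apply that wording, and four departments could apply it differently.

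**Conclusion.** The concern holds as a contradiction in the definition and handling of the primary event. The hospitalization condition and the two exit rules do not fit the 90-day window or the intention-to-treat analysis, and following the text as written can miscode recurrences reoperated during the primary stay.

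The effect is conditional. It favours false non-inferiority if the short arm is truly worse or loses more events. It vanishes in the difference if the arms and the losses are equal, and it works against the short arm if more events are lost under 24 h. Section Trial rationale expects shorter stays with shorter drainage but gives no figure, so the net direction cannot be determined.

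For an assumed common loss of 5% to 20% of recurrences, the final type I error is about 0.037 to 0.110 if coded as non-events and 0.032 to 0.068 if dropped, against a nominal 0.025. These figures rest on an assumed in-stay share and on a normal-approximation test of the risk difference. The plan names relative risk regression with likelihood ratio tests, so they indicate scale and are not error rates of the stated analysis.

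**What to change.** 1. In the Primary outcome paragraph of {18a}, delete the hospitalization condition, or add that a deterioration occurring during the primary hospitalization also qualifies. State that neurological deterioration with imaging-confirmed recurrent hematoma and a need for repeat surgery counts at any time from the end of the index operation to day 90, before or after discharge.
2. Keep the third criterion as a *need* for repeat surgery. Changing it to surgery performed would narrow the endpoint, because patients who need reoperation but die first or are not operated on would no longer count.
3. Reconcile {11b} and {17b} with this. State that meeting these criteria does not end outcome follow-up by record review (subject to withdrawal of consent) and does not remove the patient from the intention-to-treat analysis in the randomized arm. The {11b} list itself need not be rewritten.
4. State that in-stay reoperations for reasons other than recurrent hematoma are not primary events.

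Clinical handling is unchanged. The cost is protocol and eCRF wording; the planned record review already supplies the data. The observed recurrence rate may be slightly higher than under the present wording.
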